#### Mediation and moderation

A multi-level approach to mediation and moderation analyses will be used to test the hypotheses that greater improvements in self-efficacy, barriers, and social support will be found in the sequential arm (versus simultaneous arm) leading to greater improvement in behavioral outcomes. The multi-level approach examines how the SCT constructs (Fig. 2), measured over time, may influence the effect of the intervention on study outcomes and allow for the estimation of the direct association between the intervention and the outcome variable at both the between and within person levels (% study goals) [77, 78]. Indirect effects (association of intervention through SCT constructs) are estimated as the product of the coefficients linking the intervention to an SCT mediator and the intervention to the outcome [79]. A moderated mediation model will then be examined: this hypothesizes that the indirect effect of the intervention on the outcome is conditional on the level of the hypothesized moderator variable (Fig. 2) [80]. Finally, Monte Carlo bootstrapping will be used to construct 95% confidence and test for significance [81]. MPlus Version 8 software will be used (Muthen & Muthen, Los Angeles, CA) [82]. Mediation and moderation analysis will similarly be pursued using data collected at baseline and 6-month follow-up for Projects 1 and 2, though exploring effects that solely focus on either weight loss or increases in physical activity, respectively.

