**Fig. 1 Fig1:**
[figure not shown]
AMPLIFI study flow diagram

The main outcomes of the AMPLIFI project are diet quality, physical activity, and weight status. Secondary outcomes include body composition (muscle mass), physical performance, survivorship symptoms, health and health care utilization, and quality-of-life. Specific hypotheses for projects 1 and 2 are that intervention participants will have a significantly greater probability of reaching > 3% weight loss and national physical activity guidelines (≥150 weekly minutes of moderate-to-vigorous intensity aerobic physical activity), respectively, than participants in the wait-list control arm. Specific hypotheses for project 3 are that sequenced arm participants will have a significantly greater probability of achieving behavioral goals (improved diet quality, > 3% weight loss and ≥ 150 weekly minutes of moderate-to-vigorous intensity aerobic physical activity) than survivors randomized to the simultaneous arm, as participants (such as those who are older and who comprise a substantial proportion of the survivorship community) may find the combination of diet and exercise more overwhelming than approaching the health behavior changes one at a time [16, 17]. Significant mediators and moderators of treatment efficacy (e.g., self-efficacy, age, race, rural/urban status) will be identified to improve our understanding of how the intervention(s) work and for whom they work best. Lastly, the cost-effectiveness of interventions will be explored based on incremental costs per Quality Adjusted Life Years (QALYs). Assessments are performed exclusively via remote means, thus making AMPLIFI one of a handful of new generation RCTs for which accrual, intervention delivery and assessment are broadly scalable.

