#### Data analysis

Descriptive statistics will be calculated for all study variables, and normality checks will be performed with subsequent data transformation if indicated prior to data analysis. Statistical tests will be two-sided using a significance level of 5%. Statistical analyses will be conducted using SAS version 9.4 or higher (Cary, NC). Multiple imputation methods may be used to address missing data for variables with moderate amounts of missing data. Formal interim analyses and stopping rules are not planned given the relatively short duration of our intervention and primary aims of behavior change.

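### The stated indirect effect multiplies two intervention coefficients and leaves out the mediator-to-outcome path, so where the intervention moves both construct and outcome an inert construct would often be called a mediator

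*Protocol article*

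**What the plan says.** The protocol article, under Mediation and moderation, sets out a chain for Project 3: "greater improvements in self-efficacy, barriers, and social support will be found in the sequential arm (versus simultaneous arm) leading to greater improvement in behavioral outcomes". It says the multi-level approach will "allow for the estimation of the direct association between the intervention and the outcome variable", and then names the indirect effect as the association of the intervention that passes through the Social Cognitive Theory (SCT) constructs. The estimator given for that indirect effect is the "product of the coefficients linking the intervention to an SCT mediator and the intervention to the outcome".

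A moderated-mediation model follows, in which the indirect effect depends on a moderator. For inference, "Monte Carlo bootstrapping will be used to construct 95% confidence and test for significance". The approach also extends to the other two trials: "Mediation and moderation analysis will similarly be pursued using data collected at baseline and 6-month follow-up for Projects 1 and 2".

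The purpose is given with the hypotheses in the Background: "Significant mediators and moderators of treatment efficacy (e.g., self-efficacy, age, race, rural/urban status) will be identified". No section shown names a mediator-to-outcome coefficient. Fig. 2 (the conceptual model) and the reference cited for the formula cannot be inspected here.

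**The concern.** Write a for the intervention-to-mediator coefficient, b for mediator-to-outcome adjusted for the intervention, c for the total intervention-to-outcome effect and c' for the direct effect adjusted for the mediator. A product-of-coefficients indirect effect is a × b. The article describes a × c (or a × c', since it does not say which).

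That product shows only that the intervention moved two things. It cannot show that one moved the other, so it cannot test the hypothesised chain. It also conflicts with its own surroundings. The indirect effect is said to run through the constructs, and the preceding sentence assigns the intervention-outcome link to the direct association.

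At stake is the trial's account of how the interventions work. A construct could be reported as a mechanism, and carried into later programmes, merely because it changed in a trial that also changed behaviour. A real mechanism could be understated or missed.

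**Working it through.** **Algebra (linear case).** The total effect is c = c' + a × b.

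- Inert mediator (b = 0): the correct product is a × 0 = 0. The written product is a × c = a × c', which is non-zero whenever the intervention moves both variables.
- Complete mediation (c' = 0): the correct product is a × b. The written product is a × (a × b) with the total effect, and a × 0 = 0 with the direct effect.

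**Inputs from Sample size and power.**

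| Project | Analysed per arm | Planned rates | Stated power | Recomputed power |
|---|---|---|---|---|
| 1 | 130 vs 260 | 43.9% vs 27.3% | 90% | 90.4% |
| 2 | 130 vs 260 | 17.6% vs 3.8% | >95% | 98.8% |
| 3 | 260 vs 260 | 33.3% vs 22.2% | 80% | 80.9% |

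The stated powers reproduce. The article gives no figure for the mediation analysis itself.

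**Assumption, not in the article.** The intervention shifts the construct by 0.2, 0.3 or 0.5 SD, and the construct has no effect on the outcome (b = 0).

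**Simulation.** There were 2,000 trials per cell, with a normal mediator and a binary outcome depending on arm only. Path a came from linear regression, and c, c' and b from logistic regression. Each product was tested with a 95% Monte Carlo interval of 2,000 draws. This is a single-level simplification of the planned multi-level model.

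Share of trials declaring mediation by the inert construct:

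| Project | Product | 0.2 SD | 0.3 SD | 0.5 SD |
|---|---|---|---|---|
| 1 | a × c (as written) | 39% | 71% | 91% |
| 1 | a × b | 1.8% | 3.9% | 5.9% |
| 2 | a × c (as written) | 46% | 77% | 99% |
| 2 | a × b | 1.6% | 3.8% | 4.4% |
| 3 | a × c (as written) | 47% | 75% | 82% |
| 3 | a × b | 2.2% | 4.2% | 5.0% |

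Using c' in place of c changes these rates by at most about 3 percentage points. A repeat simulation at the same rates gave 40-48%, 69-79% and 83-99% across the three projects for the written product, and 1-5% for a × b. The two runs agree to within a point or two.

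**Hand check.** The written test rejects roughly when both paths are significant, so its rate is about (power for a) × (power for c).

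- Project 3, 0.3 SD: SE(a) = √(1/260 + 1/260) = 0.0877; 0.3/0.0877 = 3.42; power for a = Φ(3.42 − 1.96) = 0.928; 0.928 × 0.809 = 0.75 (simulated 75%).
- Project 1, 0.3 SD: SE(a) = √(1/130 + 1/260) = 0.1074; 0.3/0.1074 = 2.79; power for a = Φ(2.79 − 1.96) = 0.798; 0.798 × 0.904 = 0.72 (simulated 71%).

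**When a path is null.** If the construct does not move, a × c rejects in about 4-5% of trials (3-6% in the repeat run). If Project 3's outcome does not move (22.2% in both arms), it rejects in 0-5%.

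**Complete mediation.** A linear model with a = b = 0.5, c' = 0, 260 per arm and 1,000 trials has a true indirect effect of 0.5 × 0.5 = 0.25. These values are also assumptions.

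| Product | Mean estimate | Declared significant |
|---|---|---|
| a × b | 0.251 | 100% |
| a × c | 0.129 | 72% |
| a × c' | 0.000 | 5% |

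**The case against.** The strongest reply is that this is a slip of the pen. The same sentence speaks of effects through the constructs, the sentence before it treats the intervention-outcome link as direct, and the hypothesis is a chain. All three point to a × b, with the word intervention written where mediator was meant. Mediation software would normally compute a × b. This is fair, and it is the likeliest explanation. Intent cannot be confirmed, however, and the sentence states an estimator rather than leaving one to a fuller document, so the error is in the text.

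A reader might go further in four ways that the article does not support:

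- **That the rule will always declare mediation by an inert construct.** It does so only when the intervention moves both construct and outcome. That condition is not remote, since the Conceptual framework section says the interventions target these constructs and the power section assumes outcome differences in every project.
- **That false findings approach certainty throughout.** The rate depends on an assumed mediator shift. In Project 3 it is also limited by the roughly 80% power of the outcome comparison.
- **That complete mediation would necessarily be missed.** That follows only if c' is meant. With c the estimate is about half the true value in the example, but still detected in 72% of trials.
- **That the main results are at risk.** No primary or secondary arm comparison uses this product. The analysis is explanatory, and the article describes the Projects 1 and 2 version as exploring effects.

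**Conclusion.** The concern holds in this conditional form. The stated formula is not an indirect effect, and nothing in the article corrects it. If it were followed and the intervention moved both construct and outcome, an inert construct would be labelled a mediator in roughly 40% to 99% of trials, depending on project and mediator shift, against about 1-5% for a × b. With either path null, the error stays near or below about 5%. The size rests on the article's own rates and sample sizes, on assumed mediator shifts of 0.2-0.5 SD, and on a single-level model. Because the wording is probably a slip in an explanatory analysis and leaves the arm comparisons intact, it is a should-fix, not a must-fix.

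**What to change.** Replace the sentence so that the indirect effect is the product of two coefficients: intervention to SCT construct, and SCT construct to outcome from a model that also includes the intervention. Both should be estimated within the planned multi-level model. State that the Monte Carlo interval and the moderated-mediation model are built on that product, and that this applies to all three projects. Check that the Mplus specification matches. Adding baseline mediator and outcome as covariates is optional and not part of the correction.

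The cost is one sentence in the analysis section or analysis plan. It needs no new data and no change to conduct or sample size.

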#### Economic analysis

Intervention implementation costs and participants’ health care costs (based on self-reported health care utilization) will be calculated. Intervention implementation costs include mostly those of personnel for website management and updates, and supplies. Development and research-related expenses will not be included. We will also estimate intervention costs for participants, i.e., time spent on the intervention web sessions. Health care costs will be compared across arms to determine if any of the AMPLIFY interventions result in health care cost savings. We will conduct a within trial cost-effectiveness analysis to compare intervention implementation costs net of health care cost savings to the interventions’ effectiveness measured by the gain in quality-adjusted life years (QALYs) [83, 84]. QALYs will be estimated based on the utility scores of the EQ-5D [85–87]. As for the main efficacy assessment, we will compare the dietary intervention versus wait-list control (Project 1), the exercise intervention vs wait-list control (Project 2), and the sequenced vs combined interventions (Project 3). Incremental Cost-Effectiveness Ratios (ICERs) will be calculated and compared to commonly used thresholds (e.g., $50,000 per QALY) to determine which interventions are worth their costs [88]. Sensitivity analyses will examine robustness of results to assumptions such as unit cost values used for salaries or health care events, and separate analyses will examine cost-effectiveness for younger/older, rural/urban, minority/non-minority survivors.

### Dissemination plan

Investigators will communicate trial results to participants, healthcare professionals, the public, and other relevant groups via publications (in peer-reviewed scientific journals, study newsletters), presentations (to community organizations, professional societies), and reporting in Clinicaltrials.gov.

## Discussion

The current study will test the adaptation of efficacious interventions to web-based platforms for cancer survivors. It is important to determine the extent to which programs originally conceived in a research setting are amenable for wide dissemination and maintain their potential to improve survivors’ outcomes via remote delivery. This study also will be the very first to test the relative efficacy of simultaneous versus sequential approaches to promote multiple behavior change among cancer survivors. Past studies assessing multiple behavior changes in different populations have produced mixed findings [14], with some results supporting sequential approaches to multiple behavior change [17, 89], and others favoring simultaneous [90] or showing no differences [91]. Thus, programmatic research to pinpoint optimal sequencing and/or combination of multiple health behavior interventions for specific target populations will help inform future clinical practice and health promotion efforts.

Strengths in the design of this program project include integration amongst the RCTs, which allows for sharing of a control condition and research cores. Other strengths include: objective measurement of weight and aerobic physical activity (as well as the collection of physical performance, muscle mass and key circulating biomarkers); an evidence-based theoretical framework; and formal cost analyses, which will shed light on the dissemination and implementation potential of the AMPLIFI programs. In addition, the expansion of accrual of cancer survivors across the continental U.S. will further bolster the generalizability of results. At its very core, AMPLIFI builds on the success of two previously proven efficacious interventions, by using dissemination and implementation science tools to glean key user and stakeholder input and arrive at scalable interventions. The current study also moves the cancer survivorship field forward by recruiting a large, diagnosis-diverse sample and focusing on older, rural, and racial minority groups, all of which have been underrepresented in the lifestyle intervention research to date [15].

As for study limitations and/or challenges, the COVID-19 pandemic caused an initial delay in participant recruitment and necessitated the adoption of remote assessment protocols [45]. To overcome the challenge of assessment retention over the extended period of study enrollment (i.e., 2 years), we are implementing a comprehensive set of retention activities. To assuage concerns regarding potential differential drop-out between the active intervention and wait-list arms, the wait-list participants receive access to survivorship online videos designed to support health and wellbeing. Similar concerns exist regarding participant preferences or motivational readiness for specific health behaviors. For example, cancer survivors who are assigned the diet intervention first may demonstrate better retention/engagement than those assigned to exercise first. Further, engagement with the website may attenuate over time, due to the duration of the interventions. Thus, participant website engagement will be closely monitored throughout the project with patterns of engagement over time scrutinized to identify vulnerable time points that signal engagement drop off that could be addressed with minimal touch contact in future intervention implementation (e.g., additional text messaging, etc.).

AMPLIFI’s greatest scientific contribution is likely the development and adaption of efficacy-tested diet and exercise intervention content for delivery via interactive web-based platforms (as well as the refinement of remote assessments that are able to evaluate the impact of such programs). The use of innovative technology to enhance the reach of lifestyle interventions has substantial public health implications given the rising numbers of cancer survivors at risk for physical inactivity, poor diet quality and excess weight [92]. Scalable internet-based intervention strategies can help address these quality-of-life concerns, as well as cancer disparities among older, racial/ethnic minority, and rural survivors.

## Data Availability

Data sharing is not applicable to this article as no datasets were generated or analyzed yet for the current study.

## Abbreviations

AMPLIFI: Adapting MultiPLe behavior Interventions that eFfectively Improve (AMPLIFI) cancer survivor health
RENEW: Reach-out to ENhancE Wellness
BEAT: Better Exercise Adherence after Treatment for cancer
U.S.: United States
RCTs: Randomized controlled trials
QALYs: Quality adjusted life years
IRB: Institutional Review Board
SCT: Social Cognitive Theory
AMPLIFY: AiM, Plan, and act on LIFestYles
Kg: Kilogram
M: Meters
S.M.A.R.T.: Specific, Measurable, Achievable, Relevant, and Time-Bound
COVID-19: Coronavirus Disease 2019
UAB: University of Alabama at Birmingham
FORCE: Facing Hereditary Cancer Empowered
Mg: Milligram
DBS: Dried blood spot
ID: Identification
HIPAA: Health Insurance Portability and Accountability Act of 1996
NIH: National Institutes of Health
ICERs: Incremental Cost-Effectiveness Ratios
